3. If any of their family members (spouse, children etc.) have not tested for HIV in the past year. If yes, an invitation letter will be issued inviting all family members to come to the health facility for HIV testing. If any member is found HIV-positive, s/he would be invited to participate in the FAM-CARE program at the facility

Additionally, HIV-positive adults receiving care and treatment services will also be used as index cases to identify HIV-positive children for enrollment into the FAM-CARE program. Each family should have at least one HIV-positive child receiving HIV treatment services.

*Eligibility criteria for enrollment into FAM-CARE program*

- Presence of at least one child (up to the age of 15 years) who is HIV-positive and receiving care at the selected facility. A child will be enrolled if newly diagnosed as HIV-positive and not yet on ART (ART-naïve) or if already known to be HIV-positive but not yet initiated treatment (ART-naïve) or if already on treatment (ART-experienced).
- Family members (someone who is related to the child either by blood or adoption. These can include the mother, father, sister(s) and brother(s), cousins) receiving HIV care and treatment services and residing in the same household as the index child.
- Willingness to disclose HIV status to other family members.

It is estimated that the majority of HIV-positive children will have an HIV-positive family member, but a small percentage may be orphans cared for in a household without other HIV-positive children or adults. Additionally, a small percentage of mothers may not want to participate in the family-centered program because of disclosure issues. We estimate that this will not be more than 10-20% of HIV-positive children. These children would continue their care at the intervention facility but outside of the FAM-CARE program (e.g., routine pediatric or adult HIV clinics).

*Provision of FAM-CARE services*

All family members will be registered in the health facility as a family unit and will have their chronic care files kept in one family folder. Appointments for HIV care and treatment services will be made on the same day for the family as a unit. It is standard for HIV-positive pediatric patients on ART to be seen for monthly visits and ART pick-up. Decisions regarding ART initiation will be based on Swaziland national treatment guidelines.

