**Follow-up: 18 months**

Our primary endpoints of viral suppression and HIV RNA >1,000 copies/mL will be evaluated among HIV-positive children entering the study who are initiating or receiving ART. The sample size will be powered to detect a difference in viral suppression/HIV RNA >1,000 copies/mL in children receiving ART in the FAM-CARE sites to those receiving ART in control sites. For HIV-positive children entering the study who are not currently on ART, we will be able to compare retention in care and the proportion of children initiating ART between those enrolled in the FAM-CARE sites to those in control sites.

At FAM-CARE sites, it is estimated that 10-20% of HIV-positive children may not be enrolled in the FAM-CARE program, because of disclosure or other issues within the family. These children will still be enrolled in the prospective cohort as long as there is >1 family member who is also HIV-positive; we will be able to compare suppression/ART failure/retention rates between children in FAM-CARE sites enrolled in the FAM-CARE program and not enrolled in the FAM-CARE program, although the study will not be powered based on this comparison. We will also be able to compare overall rates of viral suppression/HIV RNA >1,000 copies/mL among all children (regardless of actual participation in FAM-CARE programs) seen at facilities with the FAM-CARE program to those in control facilities.

An individual family may have more than one HIV-positive child, and more than one HIV-positive child that is receiving treatment; based on a review of pediatric enrollment at two sites, it is estimated that ~15% of HIV-positive children come from families with more than one child receiving ART. Viral suppression rates in children from families with more than one child on treatment may be correlated, particularly in the FAM-CARE program. We will create a “family identification number” that will be used at both FAM-CARE and control sites to identify children enrolled in the study who come from the same family, which will allow controlling for potential correlation during analysis.

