***Recruitment***

Eligible HIV-positive children age <15 years and their caregivers from families with at least one additional HIV-positive family member residing in the household at study sites will be identified and referred by clinic staff to the site study nurse, who will explain the study and study procedures. The study nurse will conduct the informed consent procedures with eligible caregivers and informed assent discussion with older children (> 12 years to <15 years) in a private location with a witness present in the case of an illiterate participant. The informed consent form (and informed assent form when relevant) will be read to the caregiver/child and h/she will be given the opportunity to ask questions. Written informed consent will be obtained from the mother/caregiver prior to any study procedures being conducted. Mothers under the age of 18 years will be treated as mature (emancipated) minors and able to provide informed consent for themselves and their children. After obtaining written informed consent from the caregiver, the study nurse will seek verbal informed assent from children >12 to <15 years of age. Once informed consent (and informed assent as appropriate) are obtained, participants will be enrolled in the study and assigned a participant study identification number that will include a family identification designation for all enrolled family members. Enrollment will continue in each site until the targeted number of HIV-positive children have been enrolled.

Informed consent will be sought from other HIV-positive adult (>18 years) family members at both FAM-CARE and control sites for abstraction of HIV-related clinical and laboratory data from medical records. For HIV-positive adolescents between the ages of 15 through 17 years, informed consent for data abstraction from existing medical records will be obtained from the mother/caregiver. However, this will not be required to enroll a child into the study. HIV-positive adults in the family who provide informed consent will be assigned a participant study identification number that includes a family study identification designation.

*Statistical Methodology*

*Sample size estimation*

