**ii. Research Protocol/Methods**

1. ***Study Procedures***

After obtaining written informed consent from the caregiver and verbal informed assent from children < 12 years, eligible HIV-positive children will be enrolled in the study into the FAM-CARE or control arm depending on the facility h/she attends. An enrollment visit will be conducted, during which caregivers will be interviewed to collect demographic, medical and HIV-related information about the child. Clinical/laboratory data will be abstracted from clinic medical records. The caregiver will be interviewed regarding HIV infection status of other family members and clinical/treatment history obtained for other HIV-positive family members by interview and chart abstraction. Children will be seen for a study-specific visit at enrollment and every three months by study staff. Study visits will be scheduled to coincide with routine health services visits to the child as much as possible.

At each study visit, the study nurse will obtain interim clinical history (e.g., medical/HIV history and CD4 count and, for children on treatment, ART history, current regimen, and adherence questionnaire) by caregiver interview and abstraction of clinical and laboratory data from medical records and record on study data collection tools. Clinic visit attendance and pharmacy drug pick-up for children receiving ART will be obtained by chart abstraction. Blood will be drawn from the HIV-positive children on ART for study viral load testing at enrollment and at 6, 12, and 18 months on study. HIV-positive children not on ART at enrollment who initiate ART during study follow-up will have viral load testing at ART initiation and every six months during the study. Table 3 shows the proposed schedule of data collection.

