***b) Schedule of Evaluations***

**Table 5** shows the schedule of evaluations.

**Table 5.** Schedule of Evaluations

| **Data Collection** | **Forms** | **Enroll-ment** | **3 mos** | **6 mos** | **9 mos** | **12 mos** | **15 mos** | **18 mos** |
| --- | --- | --- | --- | --- | --- | --- | --- | --- |
| Informed consent caregiver-child | - Caregiver-child informed consent form | X |  |  |  |  |  |  |
| Age-appropriate assent of children > 12 years | - Verbal assent form | X |  |  |  |  |  |  |
| Informed consent for medical record abstraction from HIV-positive family members | - Family member informed consent form | X (or anytime during study) |  |  |  |  |  |  |
| Demographic data | - Enrollment Form | X |  |  |  |  |  |  |
| Family HIV history | - Enrollment Form | X |  |  |  |  |  |  |
| Treatment and viral load data for HIV-positive caregivers interview and medical record abstraction ) | - Enrollment and Follow-up Visit Form - Family Member Clinical record abstraction Form | X | X | X | X | X | X | X |
| Treatment and viral load data for HIV-positive adult family members by interview (and medical record abstraction if consent is obtained) | - Family member clinical record abstraction form | X |  | X |  | X |  | X |
| *All HIV-positive children* | | | | | | | | |
| Demographics (DOB, gender) | - Child Enrollment Form | X |  |  |  |  |  |  |
| HIV history | - Child Enrollment Form | X |  |  |  |  |  |  |
| Interim (between visits) HIV history | - Child Follow-up Form |  | X | X | X | X | X | X |
| CD4 count (program data) | - Child Clinical Record Abstraction Form | X |  | X |  | X |  | X |
| Medical visit attendance timeliness/missed visits | - Child Clinical Record Abstraction Form |  | X | X | X | X | X | X |
| *HIV-positive child receiving ART** | | | | | | | | |
| ART history | - Child Enrollment Form - Child Follow-up Form | X |  |  |  |  |  |  |
| Current ART regimen | - Child Clinical Record Abstraction Form - Child Enrollment and Follow-Up Forms | X | X | X | X | X | X | X |
| Adherence questionnaire | - Child Enrollment Form - Child Follow-up Form | X | X | X | X | X | X | X |
| Pharmacy ART pick-up | - Child Clinical Record Abstraction Form | X (if already on ART) | X | X | X | X | X | X |
| Viral load | - Blood draw | X |  | X |  | X |  | X |

*Collected any time a child is initiated on ART (on ART at entry or starts ART during study)

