All data will be aggregated or summarized so that no individual data will be presented as part of study findings in papers or at conferences. By virtue of their presence in the clinic and data abstraction activities from existing clinic records, study staff will view records of all women attending HIV care, including those not enrolled in the study. However, individual data from non-study participants will not be abstracted/collected for study purposes. Study staff will receive ethics training to ensure compliance with human subjects’ research requirements.

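### Record-abstraction consent is sought from HIV-positive adult relatives without exception, including in families not known to have disclosed, and no safeguard covers disclosure within the family

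*Protocol*

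**What the plan says.** **Who enters the study.** The FAM-CARE program has a disclosure condition: "Willingness to disclose HIV status to other family members" (Description of FAM-CARE Service Program). The same section expects that "a small percentage of mothers may not want to participate in the family-centered program because of disclosure issues". In the Subject Population text after Figure 1, the protocol estimates that 10-20% of children at FAM-CARE sites may be outside the program because of disclosure or other family issues, and says of them: "These children will still be enrolled in the prospective cohort as long as there is >1 family member who is also HIV-positive". The study's Entry Criteria for Enrollment contain no disclosure condition in either arm.

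**Who is approached.** Recruitment states: "Informed consent will be sought from other HIV-positive adult (>18 years) family members at both FAM-CARE and control sites". Study Procedures and the cohort's Informed Consent Process repeat the rule. Each adds that "this will not be required to enroll a child into the study". None exempts any family, asks for the caregiver's agreement first, or says how a relative is contacted.

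**What risk is acknowledged.** Risks and Benefits to Subjects names two potential risks, blood-draw pain and bruising and unintended disclosure of HIV status, without ranking them. That section and Steps to Minimize Risks offer coded databases, password protection, staff training, confidentiality agreements and private interviews.

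**How relatives' data are obtained.** Study Procedures has "clinical/treatment history obtained for other HIV-positive family members by interview and chart abstraction". Table 5 has "Treatment and viral load data for HIV-positive adult family members by interview (and medical record abstraction if consent is obtained", at enrolment and at 6, 12 and 18 months. A later paragraph of Study Procedures says that for relatives nothing beyond data abstraction is done.

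**The concern.** The program screens for willingness to disclose; the study does not. The cohort can therefore include families in which one adult does not know that the child, or the child's mother, is HIV-positive. The consent rule sends study staff to those adults. A request for access to a relative's HIV records, in a study that enrols HIV-positive children from the same household, could tell that relative what the caregiver chose not to. The approach itself carries the risk, so it does not help that the relative may refuse or that the child's entry does not depend on the answer.

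What is at stake is first a confidentiality harm in the families most exposed to it. Such an event might also lead a family to leave care, and loss to follow-up is a study outcome. That second step is an inference, and the documents give no rate for it.

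**Working it through.** The point rests on reading the sections together. The only arithmetic is a ceiling on its scale.

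**Step 1: can a non-disclosing family be in the cohort?** Yes.
- At FAM-CARE sites, the program criterion ("Willingness to disclose HIV status to other family members") keeps such families out of the program, but the Subject Population text keeps their children in the study if another family member is HIV-positive.
- At control sites no disclosure criterion is applied at any stage.
- The Statistical Analysis Plan section lists within-family disclosure among the candidate factors for secondary objective 2, so the protocol itself expects it to vary between enrolled families.

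**Step 2: are adult relatives in such families approached?** By the stated rule, yes. Recruitment, Study Procedures and Informed Consent Process all say that consent will be sought, at both FAM-CARE and control sites where the arms are named. No exception appears in any of the three.

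**Step 3: does knowledge in one direction imply the other?** No. The caregiver is interviewed about relatives' HIV status, so the caregiver may know that a relative is HIV-positive. Nothing in the text establishes that the relative knows the caregiver's or child's status.

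**Step 4: does a stated mitigation cover this?**
- Coded identifiers and passwords protect the database.
- Training and confidentiality agreements bind staff.
- Private rooms prevent overhearing.

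None of these governs whether a given relative should be contacted at all.

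**Step 5: scale.** Inputs: 333 children per arm, and 10-20% of children at FAM-CARE sites outside the program.
- 0.10 × 333 = 33.3, about 33
- 0.20 × 333 = 66.6, about 67

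This 33-67 is a ceiling for FAM-CARE sites, for three reasons:
- The percentage covers other issues as well as disclosure, and the disclosure share is not given.
- In the program description the same percentage includes orphans in households with no other HIV-positive member, whom the study excludes.
- Where the caregiver is the only other HIV-positive person in the household, there is no further adult to approach.

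**Step 6: the wording on relatives' data.** Set side by side, Study Procedures first names interview and chart abstraction with no consent condition, Table 5 names interview plus abstraction subject to consent, and the later Study Procedures paragraph allows abstraction only. These do not say the same thing. Recruitment, the later Study Procedures paragraph, Informed Consent Process and Table 5 agree that abstraction needs consent, so the first Study Procedures statement is the outlier on that point.

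**The case against.** The strongest reply is that the harm is inferred. No section says that a relative is told the child's or the mother's status. What a relative hears would be in the family-member consent form and the study's operating procedures, neither of which is available here. The caregiver consents before any study procedure, and relatives' consent may be obtained at any time during the study, so staff have latitude. This stands as a limit on certainty: the disclosure is foreseeable, not demonstrated. It does not remove the point, because the protocol's own rule is universal, and good wording on a form does not settle whether the relative should be approached.

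Four stronger readings are tempting and are not supported:

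- *Disclosure is the study's main risk.* The protocol lists two risks and ranks neither.
- *The interview itself discloses.* The caregiver is the person described as interviewed about relatives, interviews are private, and relatives have no study visits. A caregiver reporting what the caregiver already knows tells the relative nothing.
- *Collecting relatives' data contradicts the promise that "individual data from non-study participants will not be abstracted/collected for study purposes".* In the Confidentiality section this follows a sentence about staff seeing the records of clinic attendees who are not enrolled. In that context it does not clearly reach caregiver-reported family history.
- *The FAM-CARE ceiling can be doubled to cover controls.* The documents give no non-disclosure rate for control families.

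The missing consent condition in the first Study Procedures statement is fairly read as brevity, since the other sections supply it. It is a wording point, not a rule permitting abstraction without consent.

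**Conclusion.** The concern holds in this form: a universal rule to seek consent from HIV-positive adult relatives operates in a cohort that includes families outside FAM-CARE over disclosure and that has no disclosure criterion in either arm. Following it can produce a harm the protocol lists, and no stated mitigation addresses disclosure within the family. The conclusion assumes that an approach about this study could reveal a household member's status, which is reasonable but not stated in the text.

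The number of exposed families is unknown. At FAM-CARE sites it is at most about 33-67 children on the protocol's own percentages, and probably fewer; for control sites no figure can be given. The primary endpoints are not affected. The inconsistent wording on how relatives' data are obtained is a secondary matter of clarity.

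**What to change.** **Main change.** In Recruitment, in the relatives' consent paragraph of Study Procedures, and in Informed Consent Process, state that an adult relative is approached for record-abstraction consent only after the caregiver has confirmed, in a yes/no field on the enrolment form, that this relative knows both the child's and the caregiver's status. Otherwise no approach is made. For adolescents aged 15 to 17, consent already comes from the caregiver, so this change does not concern them.

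**Wording change.** Reconcile the first Study Procedures statement and Table 5 with the later paragraph. Say that chart abstraction requires the relative's consent and that the interview is the caregiver's own report.

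**Cost.** One form field and a few sentences. Some relative-level covariates for secondary objective 2 will be missing, and the gaps will concentrate in non-disclosing families, so they will not be random. The new field identifies those families, and caregiver report still supplies part of the information. Child enrolment, sample size and the primary endpoints are untouched, because a relative's consent is not needed for the child to enter.

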In a recent large cross-sectional survey in Malawi and a 2013 systematic review of viral suppression in HIV-positive adults on ART, viral suppression to RNA <1,000 ranged between 61.8-71.2% (intention-to-treat analysis) (16,17). Data on virologic outcomes for children on ART in sub-Saharan Africa are limited. In a cross-sectional survey of viral suppression (RNA <80 copies/mL) among children on first-line ART for > 6 months in 10 nurse-led clinics in Lesotho, viral suppression was found in only 72.3% of 191 children; no predictors for viral outcome were identified (18). Similarly, in a study of 742 HIV-positive children initiating first-line ART in South Africa between 2008-2011, only 62.3% achieved a viral load <50 copies/mL 6 months after ART initiation (19). Somewhat better data on short-term viral response were reported among a small cohort of 69 HIV-positive children initiating ART in Zambia, with 88.5% having viral suppression (RNA <400 copies/mL) at 6 months, but this decreased to 77.8% by 24 months (20). In a descriptive study using data from a pilot program in 2012-2013 of routine viral load monitoring in 12,063 HIV-positive persons (including 580 children <10 years and 588 adolescents 10-19 years) in Shiselweni, Swaziland, 16% were found to have detectable viral load (>100 copies/mL); children had a 2.6-fold and adolescents a 3.2-fold increased odds of having a detectable viral load (29% of children <10 years and 35% of adolescents 10-19 years had detectable viremia) and were less likely to re-suppress at re-testing after adherence counseling (21). Thus, the available pediatric data suggests viral suppression below the level of assay quantification (RNA <50-400 copies/mL) is observed in 62-78% of children after >6-24 months of ART. In a pooled analysis of data from 5,485 HIV-positive children who initiated ART at 7 South African treatment programs with viral load monitoring, the probability of having a single viral load measurement >1,000 copies/mL was 16.9% at 1 year (95% CI 15.8-18.1) and 32.1% (95% CI 30.2-34.1) at 3 years after starting ART; the frequency of ART failure (two viral load >1,000 copies/mL) was 19.3% by 36 months (22). There are many factors that contribute poor overall virologic response to ART and problems with retention and ART adherence in children, many of which stem from the fact that children are dependent upon adults administration of their medications and attendance at clinic appointments; a family-focused program of care may serve to improve both pediatric retention in care and viral suppression.

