The primary study endpoints are the proportion of children on ART with viral suppression (defined as HIV RNA below the level of assay detection) and the proportion with HIV RNA >1,000 copies/mL at 18 months. The tables below show the minimum number of children receiving ART needed to demonstrate significant (0.05) effects of the FAM-CARE program on viral suppression and HIV RNA >1,000 copies/mL compared to control facility care, assuming different viral suppression and HIV RNA >1,000 copies/mL rates in the control group.

**Table 3** (viral suppression) shows the minimum sample size per arm and overall needed to demonstrate a significant FAM-CARE program effect with 80% power at 5% significance levels, assuming different levels of viral suppression in children on ART from control facilities (ranging between 65-85% suppression) and different levels of improvement that could be observed in children in FAM-CARE program sites compared to control sites. With 398 HIV-positive children receiving ART from unique families, we will have 80% power to detect at least a 10% increase in viral suppression with FAM-CARE, assuming a viral suppression rate between 65% and 80% in control children on ART.

**Table 3.** Sample size estimates for detecting FAM-CARE effects on viral suppression rates

| % Viral Suppression in Control | Minimum Effect of FAM-CARE | % Viral Suppression in FAM-CARE Sites | Alpha | Power | Sample size/ arm | Total sample size | Adjusted for 10% LTFU |
| --- | --- | --- | --- | --- | --- | --- | --- |
| .65 | .15 | .80 | .05 | 80% | 138 | 276 | 308 |
| .65 | .20 | .85 | .05 | 80% | 73 | 146 | 164 |
| .65 | .25 | .90 | .05 | 80% | 43 | 86 | 96 |
| .70 | .15 | .85 | .05 | 80% | 121 | 242 | 270 |
| .70 | .20 | .90 | .05 | 80% | 62 | 124 | 138 |
| .75 | .15 | .90 | .05 | 80% | 100 | 200 | 224 |
| .80 | .10 | .90 | .05 | 80% | 199 | 398 | 444 |
| .85 | .05 | .90 | .05 | 80% | 686 | 1372 | 1526 |

**Table 4** (HIV RNA >1,000 copies/mL) shows the minimum number of children required to detect at least a 5%, 10%, or 15% improvement with FAM-CARE care sites compared to control sites, with 80% power at 0.05 significance level, assuming different HIV RNA >1,000 copies/mL rates in control children (ranging from 10-30%).

**Table 4:** Sample size estimates for detecting FAM-CARE effects on HIV RNA >1,000 c/mL

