| % HIV RNA >1,000 c/mL in Control | Minimum Effect of FAM-CARE | % HIV RNA >1,000 c/mL in FAM-CARE Sites | Alpha | Power | Sample size/ arm | Total sample size | Adjusted for 10% LTFP |
| --- | --- | --- | --- | --- | --- | --- | --- |
| .10 | -.05 | .05 | .05 | 80% | 435 | 870 | 968 |
| .15 | -.05 | .10 | .05 | 80% | 686 | 1372 | 1526 |
| .15 | -.10 | .05 | .05 | 80% | 141 | 282 | 314 |
| .20 | -.05 | .15 | .05 | 80% | 906 | 1812 | 2014 |
| .20 | -.10 | .10 | .05 | 80% | 199 | 398 | 444 |
| .20 | -.15 | .05 | .05 | 80% | 76 | 152 | 170 |
| .25 | -.10 | .15 | .05 | 80% | 250 | 500 | 556 |
| .25 | -.15 | .10 | .05 | 80% | 100 | 200 | 244 |
| .30 | -.10 | .20 | .05 | 80% | 294 | 588 | 654 |
| .30 | -.15 | .15 | .05 | 80% | 121 | 242 | 270 |

We have adjusted the effective sample size to account for a possible 10% loss to follow up over the 18-month study period. Our estimation assumes enrolment of one HIV-positive child on ART per household and that there is no correlation of children’s viral load outcomes within facilities.

Assuming 10% loss to follow-up, we plan to enroll 444 HIV-positive children receiving ART from unique family units into the study over 12 months. With this sample size, we have power to detect a minimum of 10% increase from an estimated proportion of viral suppression of 80% in the control sites to 90% in the FAM-CARE sites or 15% increase in viral suppression with FAM-CARE if control rate of suppression is 75% or lower (Table 3 highlighted rows) and a minimum reduction in HIV RNA >1,000 copies/mL rates from 20% in the control sites to 10% in the FAM-CARE sites or from 15% in the control sites to 5% in the FAM-CARE sites (Table 4 highlighted rows).

*Study sampling procedures*

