Caregiver-child pair information will be collected through caregiver interviews and review of facility, laboratory and patient records. Study nurses will be trained to interview caregivers and abstract data from the facility records using electronic data capture forms. Participant-specific data collection forms will be identified with the participant’s unique study identification number. Participant names will not be included in the study database. All electronic tablets will be password protected, with access to only key study personnel.

*3. Statistical Analysis Plan*

First, we will summarize baseline characteristics of participants using means (standard deviations) or medians (IQR) for continuous variables and proportions for categorical variables, stratified by FAM-CARE/control arms. We will identify characteristics that differ significantly between the two study arms. Since participation in the FAM-CARE program is voluntary, we will assess for potential selection bias in the FAM-CARE sites by comparing characteristics of families that decline to families that accept FAM-CARE.

The primary objective of this study is to evaluate the effect of a FAM-CARE program of HIV care on the proportion of HIV-positive children on ART with viral suppression (defined as viral load below the level of assay detection) and the proportion of HIV-positive children on ART with HIV RNA >1000 copies/mL 18 months after enrollment. We will estimate the respective proportions and associated confidence intervals by study arm. Below we outline potential approaches to estimating the effect of FAM-CARE depending on comparability of the study arms:

a) If the FAM-CARE program decline rate is low (say, <10%) and baseline characteristics of children in FAM-CARE and control sites are fairly similar, we will estimate the proportion of HIV-positive children on ART with viral suppression and associated confidence intervals by study arm. Using a simple chi-square test, we will compare the two proportions at 5% significance level. The proposed chi-square test assumes outcomes from enrolled children are independent.

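### 398 children give 80% power for a 10-point gain in viral suppression only if the control rate is 80%, not across the stated 65% to 80%

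*Protocol*

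**What the plan says.** Three places in the Protocol's Sample size estimation section bear on this point.

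- **Text above Table 3.** The sentence begins "With 398 HIV-positive children receiving ART from unique families, we will have 80% power" and goes on to claim "80% power to detect at least a 10% increase in viral suppression with FAM-CARE, assuming a viral suppression rate between 65% and 80" per cent.
- **Tables 3 and 4.** Table 3 has one row with a 10-point gain, control 80% against FAM-CARE 90%: "80 | .10 | .90 | .05 | 80% | 199 | 398 | 444". Its rows at 65%, 70% and 75% all use gains of 15 points or more. Table 4, for HIV RNA >1,000 copies/mL, has 10-point rows for 25% to 15% (250 per arm, 500 in total) and for 30% to 20%: "30 | -.10 | .20 | .05 | 80% | 294 | 588 | 654".
- **Paragraph below Table 4.** With 444 enrolled, it claims power for 80% to 90%, "or 15% increase in viral suppression with FAM-CARE if control rate of suppression is 75% or lower".

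In Background and Rationale, the protocol sums up the paediatric literature by saying that suppression below assay quantification "is observed in 62-78% of children after >6-24 months of ART".

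**The concern.** The variance of a proportion grows as the proportion moves towards 50%. A fixed 10-point difference is therefore harder to detect at a control rate of 65% than at 80%, and one sample size cannot give 80% power for it over the whole range. If 398 is just enough at 80%, it is too few everywhere below.

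A reader of the sentence above Table 3 would believe that a 10-point gain is covered wherever the control rate falls between 65% and 80%. Most of that range lies inside the 62% to 78% that the protocol draws from the literature. A true 10-point benefit would then be missed more often than the stated 20% of the time, and a null result would be read with more confidence than the design supports.

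**Working it through.** **Inputs**

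- Significance level and power: "needed to demonstrate a significant FAM-CARE program effect with 80% power at 5% significance levels" (text above Table 3).
- Test: "Using a simple chi-square test, we will compare the two proportions at 5% significance level" (Statistical Analysis Plan section of the protocol). Sidedness is not stated in words; two-sided is inferred because it reproduces the tables.
- Evaluable sample: 398, that is 199 per arm.
- Loss to follow-up 10%, and no correlation within facilities (text below Table 4).

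**Formula.** With control rate p1, FAM-CARE rate p2, d = p2 − p1 and p̄ = (p1 + p2)/2:

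n per arm = [1.960 √(2p̄(1−p̄)) + 0.842 √(p1(1−p1) + p2(1−p2))]² / d²

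**Step 1: reproduce the protocol's figure.** For 80% versus 90%, p̄ = 0.85:

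n = [1.960 × √0.255 + 0.842 × √0.25]² / 0.01 = (0.990 + 0.421)² / 0.01 = 198.96, rounded up to 199.

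The same formula matches the per-arm size in all 8 rows of Table 3 and all 10 rows of Table 4. For 80% versus 90%, a one-sided test would give 157 and a continuity correction 219, so neither is what the protocol used. For losses, 199/0.9 = 221.1, rounded up to 222 per arm, gives the stated 444.

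**Step 2: the same formula at lower control rates.** For 70% versus 80%, p̄ = 0.75:

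n = [1.960 × √0.375 + 0.842 × √0.37]² / 0.01 = (1.200 + 0.512)² / 0.01 = 293.2, rounded up to 294.

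**Step 3: power with 199 per arm.** Power = Φ{[d√n − 1.960 √(2p̄(1−p̄))] / √(p1(1−p1) + p2(1−p2))}. For 70% versus 80% this is Φ[(1.4107 − 1.2002)/0.6083] = Φ(0.346) = 63.5%.

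Results for a 10-point gain:

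| Control rate | n per arm for 80% power | Total | Power with 199 per arm | Gain detectable with 80% power, 199 per arm |
|---|---|---|---|---|
| 65% | 329 | 658 | 58.6% | 12.7 points |
| 70% | 294 | 588 | 63.5% | 12.0 points |
| 75% | 250 | 500 | 70.5% | 11.1 points |
| 78% | 221 | 442 | 75.9% | 10.5 points |
| 80% | 199 | 398 | 80.0% | 10.0 points |

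**Step 4: compare with Table 4.** The formula gives the same n when each proportion p is replaced by 1 − p. Table 4's 25% to 15% row (500) is therefore the 75% to 85% case, and its 30% to 20% row (588) is the 70% to 80% case. Both totals exceed the 398 said to be enough. Table 4 has no 35% to 25% row, so the 658 at 65% rests on the calculation alone.

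**Step 5: other readings of the sentence**

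- All 444 enrolled children evaluable (222 per arm): power is 63%, 68% and 75% at control rates of 65%, 70% and 75%.
- One-sided 5% test: 70.4% at 65% and 74.6% at 70%. It reaches 80.4% at 75%, but it does not reproduce the tables.
- A relative 10% increase: power runs from 28% at 65% to 59% at 80%.

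None makes the claim true over 65% to 80%.

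**Step 6: a slip in Table 4.** The 25% to 10% row inflates 200 to 244. Table 3 inflates the same 200 to 224 (100/0.9 = 111.1, rounded up to 112 per arm). The 244 should be 224.

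**The case against.** The strongest reply is that the correct statement already stands below Table 4, where the enrolment target is set: 10 points from 80%, or 15 points at 75% or lower. Table 3 supports it, with 398 for the first case and 200, 242 and 276 for 15 points at 75%, 70% and 65%. On this view the sentence above Table 3 is a loose summary of the table, since every row with a control rate of 65% to 80% has a gain of at least 10 points and a total of at most 398. Correcting it changes no sample size, endpoint or analysis. This stands: the error is in the stated claim, and the text below Table 4 needs no correction.

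Two further points have some force. The 62% to 78% is a literature summary with mixed assay thresholds, whereas the protocol's own estimate for the control sites is 80%; whether 80% is optimistic is a separate question. Table 4 concerns a different endpoint, so it contradicts the sentence through the symmetry of the formula, not by direct statement.

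Finally, all enrolled children enter the analysis, not one per family. With 666 enrolled, 85% on ART and 10% lost, 666 × 0.85 × 0.90 is about 509, or 255 per arm, slightly above the 250 needed for 75% versus 85%. This ignores correlation between siblings, does not reach the 294 or 329 needed at 70% and 65%, and does not rescue a sentence that is expressly about 398 children from unique families.

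**Conclusion.** The sentence above Table 3 is wrong as written. With 398 evaluable children, power for a 10-point gain falls from 80.0% at a control rate of 80% to 58.6% at 65%, and it is below 80% at every control rate in the 62% to 78% literature range (75.9% at 78%). The protocol thus gives two incompatible detectable effects for the same sample and the same primary endpoint. The narrower one, below Table 4, is right.

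These figures rest on a two-sided 5% test, equal arms and the protocol's own assumption of independent outcomes. Positive correlation within facilities or families, which its analysis section allows for, would lower power further. The planned 444 remains correct for 80% versus 90%.

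**What to change.** 1. Replace the sentence above Table 3 with one stating that, if outcomes are independent, 398 evaluable children give 80% power to detect a gain of 10.0 points at a control rate of 80%, 11.1 points at 75%, 12.0 at 70% and 12.7 at 65%. This then agrees with the paragraph below Table 4, which can stay as it is.
2. Preferably add the 10-point rows to Table 3, so that the limit is visible (per arm / total / adjusted for 10% loss): 65% to 75%, 329 / 658 / 732; 70% to 80%, 294 / 588 / 654; 75% to 85%, 250 / 500 / 556. This helps the reader but is not essential to the correction.
3. In Table 4, 25% to 10% row, change the loss-adjusted total from 244 to 224.

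The cost is protocol wording and a less favourable stated figure. The enrolment target need not change if the team keeps 80% versus 90% as its design case. If it wants 80% power for 10 points at a lower control rate, the totals in item 2 replace the 444.
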